**Method/Design:**

To test the hypotheses, all patients seeking help from the Crisis Intervention & Brief Therapy Team over a two-year period will be followed throughout their treatment up to a maximum of six months and a follow-up period of three months after ending the treatment. Patients are randomly assigned to two conditions: treatment without feedback and treatment with immediate feedback for each session. The therapists all operate in both conditions and so they deliver both treatments. An estimated total of 180 patients, aged 18 years and over, will be included in the study.

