### Randomisation

When entering the treatment facility, patients will be randomly assigned to one of both conditions. Randomisation is performed by a member of the research team before contact with the therapist takes place. There is no assessment for eligibility, all patients referred to the CI&BT team will be included in the study. Though, after the first or second assessment session, a substantial part of the clients is being referred to other services, for instance send to their GP or admitted to a hospital. Only a limited group of clients will be indicated to continue treatment at the CI&BT team. Those who continue treatment after two assessment sessions form the group that is subject to this study. At first contact it is not clear whether a client will be referred to other services or taken into treatment at the CI&BT team, while treatment has already started the moment this becomes clear. As a consequence, only after two sessions it is evident which patients will participate in the definite research condition.

So, a substantial group of randomised patients will be excluded. This post-randomisation exclusion is inevitable, given the nature of the service. Excluding patients from an analysis does not necessarily bias the results, provided that certain requirements are met, for instance that intention-to-treat applies to all randomised patients [49]. Baseline characteristics of all patients, such as gender, ethnicity, education, marital status, diagnosis and level of functioning, shall be analysed to make sure selective exclusion does not bias the results.

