#### Procedures and time points

Initial assessment (the 'baseline measurement') takes place when patients first come into contact with the Crisis Intervention & Brief Therapy Team. The intervention lasts a maximum of six months and stops when treatment ends or after six months.

The PCOMS questionnaires are completed and discussed at every session in the EXP condition. In the TAU condition, every six weeks the ORS form is completed and handed over to a research assistant, without discussing it with the therapist. In both conditions, starting at the time of the baseline measurement, additional questionnaires (BSI, HAQII) are completed by patients in both conditions after 6 weeks, 12 weeks, 18 weeks and 24 weeks of treatment. The therapist also completes questionnaires at the same point in time (6, 12, 18 and 24 weeks after treatment starts) about the course of treatment (CGI) and the alliance (HAQII). When treatment ends, all questionnaires are being completed once again. The follow-up measurement takes place three months after the end of treatment.

Before the study starts, the therapists are required to complete a one-off questionnaire measuring their attitude to the instrument and their motivation with respect to the use of feedback in general. The same questionnaire will be completed by the therapists after the study period.

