### Setting

The setting for this study is a Mental Health Crisis Intervention & Brief Therapy team (CI&BT team) in a large city, where patients with severe psychiatric and psychosocial problems come into contact with the CI&BT team during crisis. Therapists in this team are treating these patients on an outpatient basis for a period of a maximum of six months after the crisis.

Clients of different ages – with a minimum of 18 years – are referred by GPs, self-employed therapists, mental health outpatient clinics and the police. Treatment is given at the centre of the CI&BT team. There is no diagnostic screening beforehand: the CI&BT team starts immediately on a combination of diagnosis and treatment.

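### The baseline-characteristics check cannot make sure that exclusion after two sessions is unbiased, and it relies in part on diagnosis, which appears to be made after allocation

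*Protocol article*

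**What the plan says.** All statements are from the protocol article.

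- **Timing of allocation (Randomisation).** "Randomisation is performed by a member of the research team before contact with the therapist takes place".
- **Who is analysed (Randomisation).** "Those who continue treatment after two assessment sessions form the group that is subject to this study". The consequence is acknowledged: "So, a substantial group of randomised patients will be excluded". No number is given.
- **The safeguard (Randomisation).** "Baseline characteristics of all patients, such as gender, ethnicity, education, marital status, diagnosis and level of functioning, shall be analysed", and the stated purpose is that this is done "shall be analysed to make sure selective exclusion does not bias the results". The section also cites, as an example of a condition for unbiased exclusion, that intention-to-treat covers everyone randomised.
- **When diagnosis is made (Setting).** "There is no diagnostic screening beforehand: the CI&BT team starts immediately on a combination of diagnosis and treatment".
- **What happens in the sessions (Procedures and time points).** "The PCOMS questionnaires are completed and discussed at every session in the EXP condition". In TAU the ORS is completed every six weeks and is not discussed with the therapist.
- **Who treats (abstract, Method/Design).** "The therapists all operate in both conditions and so they deliver both treatments".

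**The concern.** A check on measured characteristics can reveal selective exclusion. It cannot show that there is none. That limit matters here because the exclusion comes after randomisation and after the arms have begun to differ, and the people involved in deciding who stays know the arm. Feedback in the first two sessions could change who is referred on, who is kept and who returns. If it does so in relation to prognosis, the retained arms are no longer comparable, and nothing ensures that the listed characteristics will show it.

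The list also calls diagnosis a baseline characteristic. A variable recorded after allocation by staff who know the arm could itself be affected by allocation, so it could hide an imbalance or create one.

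At stake is what the trial may claim. If the comparison looks reassuring, the sentence as written licenses the conclusion that selection bias has been excluded. The data would support only the statement that none was seen on the characteristics measured.

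**Working it through.** **1. Sequence of events, from the article**

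| Step | Where stated |
|---|---|
| Patient is randomised before therapist contact | Randomisation |
| Team starts diagnosis and treatment together, without prior diagnostic screening | Setting |
| EXP patients complete and discuss ORS and SRS at every session; TAU patients do not | Experimental intervention; Procedures and time points |
| After the first or second session many patients are referred on; continuers form the study group | Randomisation |

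Two things follow. Diagnosis by the team comes after allocation; this is inferred from Randomisation and Setting together, as no single sentence says it. The decision to retain comes after up to two sessions that differ by arm. This takes 'every session' to include the assessment sessions, which fits the remark under Randomisation that treatment has already begun by the time it is clear who will stay.

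**2. What each possible comparison can show**

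The article does not say which groups are compared.

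- *All randomised patients, EXP versus TAU.* On characteristics fixed before allocation, randomisation makes these alike apart from chance. The comparison says nothing about exclusion.
- *Excluded versus retained, arms pooled.* This shows whether exclusion is selective, but not whether the selection differs between arms.
- *Retained EXP versus retained TAU.* This is the informative one, but only for the characteristics measured.

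None of the three can establish that there is no bias.

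**3. The article's own figure**

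Sample size calculation: 90 per arm, one-sided 0.05, means 1.0 and 1.3, SD 0.80. Power = Φ(0.30 / (0.80 × √(2/90)) − 1.645) = Φ(2.516 − 1.645) = 80.8%. The stated 80% reproduces and is not affected by this point.

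**4. Illustration: how easily an imbalance would be missed**

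Assumption, not in the article: the check is a two-sided 5% test between the retained arms, 90 each.

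- Continuous measure, true imbalance 0.2 SD: Φ(0.2/√(2/90) − 1.960) = Φ(1.342 − 1.960) = 27% power, so 73% undetected. For 0.1 and 0.3 SD, 90% and 48% go undetected.
- Proportions 21% versus 11% (21% is the psychotic-disorder share under Participants; 11% is assumed): standard error under the pooled 16% = √(2 × 0.16 × 0.84/90) = 0.0547; unpooled √((0.21 × 0.79 + 0.11 × 0.89)/90) = 0.0541; power = Φ((0.10 − 1.960 × 0.0547)/0.0541) = 45%.

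**5. Illustration: what an imbalance could do to the result**

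Assumptions: baseline GSI differs by 0.2 SD, SD 0.80 at both times, baseline to week-12 correlation 0.5.

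- Unadjusted week-12 difference: 0.2 × 0.80 × 0.5 = 0.08 GSI points; 0.08/0.30 = 27% of the planned difference.
- Change from baseline: 0.08 − 0.2 × 0.80 = 0.08 − 0.16 = −0.08, the same size with the opposite sign.
- Baseline GSI as a covariate: about zero for this component.

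**6. Illustration: selection on an unmeasured factor**

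Simulation, 2,000 trials per setting, true effect zero. TAU retains 40% at random. EXP retention depends on an unmeasured prognostic factor (log-odds 0.3 or 0.5 per SD) that correlates 0.5 in size with GSI, better prognosis going with lower GSI. The first 90 retained per arm are analysed by a one-sided 5% t-test. One measured characteristic correlates 0, 0.3 or 0.5 with the hidden factor.

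| Log-odds per SD | Spurious GSI difference | Type I error | Type I error when that characteristic shows p ≥ 0.05 |
|---|---|---|---|
| 0.3 | about −0.07 | 0.14 | 0.13 to 0.14 |
| 0.5 | −0.11 to −0.12 | 0.24 to 0.25 | 0.23 to 0.25 |

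That characteristic shows p ≥ 0.05 in 85% to 94% of these trials. All six tested together do so in 66% to 73%, against 72% to 74% with no selection at all. A reassuring check therefore barely lowers the error rate under these assumptions.

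**The case against.** The strongest reply is that little of the above is in the article. It says only that characteristics will be analysed. It sets no test, threshold or pass rule, and a condensed article may leave such detail to an analysis plan. That stands, and it limits the size of the point. It does not rescue the sentence, because no choice of test or variable would let a comparison of measured characteristics make sure of the absence of bias.

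Four stronger readings are tempting and are not supported.

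- *That the safeguard rests on diagnosis.* Diagnosis is one of six examples, and gender, ethnicity, education and marital status cannot be altered by allocation. Nor does the article give evidence that two sessions of feedback would change a principal diagnosis. What stands is that it should not count as a baseline balance variable.
- *That baseline GSI is left out.* The list is open, introduced by 'such as', so GSI is not excluded. Procedures and time points puts the baseline measurement at first contact with the team, without saying that it precedes allocation, or that patients referred on early complete the BSI.
- *That a non-significant comparison will be taken as proof.* The article states no significance test. The 45% and 27% power figures belong to an assumed one, and to a comparison of retained patients only.
- *That the trial result would be off by 0.08 GSI points.* Primary analysis plans a repeated-measures GLM comparing each follow-up with baseline, not an unadjusted week-12 contrast. Under the same assumptions the shift changes sign or disappears, depending on how baseline enters.

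It can also be said that the exclusion is justified as unavoidable in this service, and that the check is only an addition. That is fair. It is still the only concrete safeguard described, since the cited intention-to-treat condition sits beside a study group limited to continuers.

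**Conclusion.** The point holds in limited form. The article claims more for the check than it can deliver: exclusion is decided after randomisation, after sessions that differ by arm, among therapists who know the arm, and comparison on measured characteristics cannot exclude bias from that. The check also relies in part on a variable that, by implication, is recorded after allocation.

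The size and direction of any bias cannot be derived from the article, which gives no exclusion rate, no rate by arm and no baseline to follow-up correlation. The numerical results show that a reassuring check and a real imbalance can coexist. They do not show that this will happen here, and they do not describe the planned primary analysis. The conclusion rests on two inferences: that diagnosis follows allocation, and that feedback is already in use during the assessment sessions.

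**What to change.** Amend the safeguard under Randomisation as follows.

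1. State that the analysis will assess selective exclusion, in place of the claim to make sure that it causes no bias.
2. For all randomised patients, report by arm the proportion excluded after the first or second session, and the reasons.
3. Compare retained with excluded patients within each arm, and retained patients between arms. Use standardised differences on characteristics that allocation cannot affect: gender, ethnicity, education, marital status and referral route. Add baseline GSI where it was obtained before the first session. Level of functioning can be handled in the same way, since the article does not say who rates it or when.
4. Report diagnosis as description only, not as evidence of balance.
5. Add a sensitivity analysis that weights retained patients by the inverse of their estimated probability of being retained, fitted by arm, and state that it covers measured factors only.

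The cost is a little extra analysis, mainly on data that the plan already collects, and a weaker stated assurance. Two items need confirming: that reasons for exclusion are recorded by arm, and how many early-referred patients have a BSI before the first session. If few do, baseline GSI can serve only in the comparison of retained patients.

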#### Procedures and time points

Initial assessment (the 'baseline measurement') takes place when patients first come into contact with the Crisis Intervention & Brief Therapy Team. The intervention lasts a maximum of six months and stops when treatment ends or after six months.

The PCOMS questionnaires are completed and discussed at every session in the EXP condition. In the TAU condition, every six weeks the ORS form is completed and handed over to a research assistant, without discussing it with the therapist. In both conditions, starting at the time of the baseline measurement, additional questionnaires (BSI, HAQII) are completed by patients in both conditions after 6 weeks, 12 weeks, 18 weeks and 24 weeks of treatment. The therapist also completes questionnaires at the same point in time (6, 12, 18 and 24 weeks after treatment starts) about the course of treatment (CGI) and the alliance (HAQII). When treatment ends, all questionnaires are being completed once again. The follow-up measurement takes place three months after the end of treatment.

Before the study starts, the therapists are required to complete a one-off questionnaire measuring their attitude to the instrument and their motivation with respect to the use of feedback in general. The same questionnaire will be completed by the therapists after the study period.

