Taking into account all considerations mentioned before, the research questions for this study are:

1) to examine whether applying immediate feedback at each treatment session in a psychiatric population with severe distress results in better outcomes (10% fewer complaints, enhanced well-being), higher client satisfaction and a more efficient treatment (shorter treatment duration) compared with the no-feedback condition (the same therapists operating in both conditions). Outcome has to be measured with a measure independent from the instrument used in the feedback process.

2) to examine whether applying immediate feedback at each treatment session results in improvements to the alliance; and whether there is a link between any improvement in alliance and improvement in treatment outcome. Alliance to be measured with a measure independent from the instrument to be used for feedback.

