#### Primary analysis: EXP versus TAU

In the primary analysis, outcomes of the two treatment conditions will be compared using repeated measures analysis (GLM), with the number of sessions as a covariate. In this analysis, each follow-up measurement will be compared separately to the baseline measurement. Since in this design patients are nested within therapists, these nested data will also be examined in a multilevel analysis, controlling for therapist variation. The number of sessions will be included as a covariate.

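### The BSI is timed by weeks of treatment, so on the best-supported reading patients who finish before week 12 have no score at the time point on which the trial is powered

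*Protocol article*

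**What the plan says.** Under Procedures and time points, the patient questionnaires (BSI, HAQ-II) start at baseline and "are completed by patients in both conditions after 6 weeks, 12 weeks, 18 weeks and 24 weeks of treatment". The therapist forms fall at the same points, described as "6, 12, 18 and 24 weeks after treatment starts". Two further assessments are tied to the end of treatment: "When treatment ends, all questionnaires are being completed once again", and "The follow-up measurement takes place three months after the end of treatment".

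Treatment length is not fixed: "The intervention lasts a maximum of six months and stops when treatment ends or after six months". The Abstract (Method/Design) says that patients "will be followed throughout their treatment up to a maximum of six months and a follow-up period of three months after ending the treatment". The Naturalistic setting section adds that duration differs considerably between patients in both conditions.

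Research question 1, at the end of the Background, expects feedback to give "a more efficient treatment (shorter treatment duration") than no feedback.

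The Sample size calculation uses the GSI at 12 weeks, with 90 patients per group, means of 1.0 and 1.3, SD 0.80, one-tailed alpha 0.05 and 80% power, and it promises intention to treat. Under Primary analysis, outcomes "will be compared using repeated measures analysis (GLM"), with each follow-up compared separately with baseline. A multilevel analysis is added for the nesting of patients within therapists.

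**The concern.** If the week-based questionnaires run only while treatment runs, a patient who finishes at week 8 gives a baseline, a week-6 and an end-of-treatment score, and a follow-up at about week 21 (8 + 13), but nothing at week 12. The week-12 comparison then covers only patients still in treatment. Whether a patient is still in treatment at week 12 is decided after randomisation, plausibly depends on how the patient is doing, and is something the trial itself expects feedback to change. Such a comparison is not the intention-to-treat comparison that the plan promises, and it rests on fewer than 180 patients.

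The other two assessments do not fill the gap. They fall at times that depend on treatment length: a patient treated for 24 weeks has end-of-treatment and follow-up scores at about weeks 24 and 37, against 8 and 21 in the example. If treatment is shorter under feedback, the arms are measured at different average times since the crisis, and feedback is mixed with natural recovery. No analysis plan can recover week-12 scores that were never collected.

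**Working it through.** **1. What the schedule yields.** The patient forms are counted in weeks of treatment, the Abstract limits observation to treatment plus three months, and a separate form is completed when treatment ends. Nothing adds a week-12 form for a patient already discharged, or says that the end-of-treatment score stands in for it.

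**2. The plan's own power.** Inputs from the Sample size calculation: difference 0.30, SD 0.80, n = 90 per arm, one-tailed alpha 0.05 (z = 1.645).

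Power = Φ(δ / (σ√(2/n)) − 1.645) = Φ(0.30 / 0.1193 − 1.645) = Φ(0.871) = 0.808 (0.805 with the t distribution).

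The stated 80% reproduces, but only with a week-12 GSI in all 180 patients.

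**3. Power when fewer are measured.** The documents give no share still in treatment at week 12, so the shares are assumptions. The difference is held at 0.30 and the SD at 0.80.

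| Share measured, each arm | n per arm | Power, normal | Power, t |
|---|---|---|---|
| 100% | 90 | 0.808 | 0.805 |
| 70% | 63 | 0.677 | 0.673 |
| 60% | 54 | 0.619 | 0.615 |

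**4. Possible bias.** Assume that patients with lower GSI leave first, with correlation ρ between GSI and staying. For a share r still in treatment, the mean of the stayers is raised by ρσλ(r), where λ(r) = φ(c)/r and c = Φ⁻¹(1 − r). This gives λ(0.70) = 0.497, λ(0.60) = 0.644 and λ(0.50) = 0.798.

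Bias against EXP = ρ × 0.80 × [λ(EXP) − λ(TAU)].

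| Staying, TAU / EXP | ρ | Bias (GSI points) | Share of 0.30 |
|---|---|---|---|
| 70% / 60% | 0.3 | 0.24 × 0.147 = 0.035 | 12% |
| 70% / 60% | 0.5 | 0.40 × 0.147 = 0.059 | 20% |
| 70% / 50% | 0.3 | 0.24 × 0.301 = 0.072 | 24% |
| 70% / 50% | 0.5 | 0.40 × 0.301 = 0.120 | 40% |
| 70% / 70% | any | 0 | 0% |

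Power loss and bias can be combined in one scenario. At 70%/50% (63 and 45 patients) the observed difference is 0.228 or 0.180 for ρ = 0.3 or 0.5, and power is 0.43 or 0.31. With the same retention and no bias it is 0.61.

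**5. Sign.** Changing the sign of ρ, so that the worse-off leave first, changes the sign of every bias in the table: the same retention figures would then favour EXP.

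**The case against.** **The restriction is inferred.** The article never says that questionnaires stop when treatment stops. The series starts at baseline, and the therapist forms are counted from the start of treatment, which taken alone could be a fixed clock. This stands as a caveat. The patient wording, the Abstract and the separate end-of-treatment form still favour the treatment-bound reading. If a fixed clock is meant, the same edit makes that clear.

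**A reader might infer that the repeated-measures GLM in effect analyses long treatments only**, because a standard GLM across all visits drops anyone with a gap. The text does not support that: each follow-up is compared separately with baseline, so a missing week-18 or week-24 score need not remove a patient from the week-12 comparison. A missing week-12 score does. The multilevel analysis is described for therapist nesting, not for missing visits.

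**A reader might also infer that the bias must run against feedback.** That holds if improved patients leave and more of them do so under feedback. The Background also reports higher drop-out in patients who deteriorate by the third session, and premature termination where the alliance is poor. If such patients leave disproportionately under feedback, the bias favours EXP. If comparable patients leave equally in both arms, there is little bias. The direction is open.

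**Week 12 appears only in the sample size paragraph**, and early finishers do have end-of-treatment and follow-up scores, so they are not lost to the trial. Both points are correct. But week 12 is the only time point for which power is claimed. The study group is also limited to patients who continue after two sessions, which removes the very shortest contacts but not those ending between then and week 12.

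**The Conclusion section concedes** that time elapsed is hard to separate from feedback. That acknowledges the difficulty without resolving it.

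**Conclusion.** The point holds in this form. The schedule, on its best-supported reading, yields no week-12 GSI for patients whose treatment ends before week 12. The power statement needs that score in all 90 patients per arm, intention to treat is promised, and treatment length is itself a hypothesised effect of feedback.

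The loss of precision follows from arithmetic once a share is assumed: about 67% power with 70% measured and about 62% with 60%, against the 81% that the plan's inputs give. The bias is less certain. The figures of 0.04 to 0.12 GSI points (12% to 40% of the target difference) rest on assumed retention that differs by arm and on an assumed correlation. They illustrate what is possible and do not estimate what will happen. The documents do not support a claim that the trial is biased in a known direction, nor that only long treatments are analysed.

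**What to change.** **Procedures and time points.** Count the BSI assessments at 6, 12, 18 and 24 weeks from baseline or randomisation, and collect them from every patient in the study group whether or not treatment has ended. The end-of-treatment and three-month forms can stay. Moving the follow-up to a fixed date is a preference and is not needed to cure this defect.

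**Primary analysis.** Use a likelihood-based mixed model on all available BSI scores at their actual dates, including end-of-treatment and follow-up scores, and estimate the week-12 contrast from it. Report by arm how many patients have a week-12 score.

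**Patients already past these points.** The article gives an October 2009 start and two years of intake, so the schedule change may come too late for many. For them only the analysis change applies, and the 80% power should be restated for the number with a week-12 GSI.

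**Cost.** A patient finishing between weeks 6 and 12 would receive three more forms after discharge (weeks 12, 18 and 24), and one finishing before week 6 would receive a fourth. In the 70%/50% case, 27 + 45 = 72 patients leave before week 12, so about 72 × 3 = 216 forms. These are self-report questionnaires for patients who are contacted for follow-up anyway. Some non-response is to be expected. The ethics committee may need to be notified, since its view rested on the questionnaires being common practice in care. The analysis change costs only analysis time.

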**Discussion:**

The aim of this study is to make clear whether, and to what extent, systematic feedback from the patient in this target group during therapy determines the course and outcomes of therapy. We also look at whether, and to what extent, the quality of the alliance and the motivation of the person delivering treatment with respect to the instruments play a role.

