## Methods

### Design

The study is a randomised controlled trial covering all patients presenting to the Crisis Intervention & Brief Therapy team over a period of two years (starting October 2009). When patients are presented to the CI&BT team, they are randomised to the experimental condition (EXP) or the control condition (TAU). The EXP condition uses an immediate feedback method for each treatment session; the TAU group does not use formalized feedback.

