Treatment is delivered in the community as much as possible. The basic philosophy of the CB&BT team involves supplying 'system-oriented tailored care': the optimal combination and intensity of interventions is established for each client system. These can vary during the course of the treatment. Treatment continuity is a goal; treatment is delivered as much as possible by the same two therapists. The therapists come from different disciplines: doctors (residents), psychiatrists, psychologists and psychiatric nurses. The core team consists of experienced therapists. The team is supplemented by a group of residents that changes every six months. The primary focus of the treatment is to help clients regain a sense of mastery over their lives again. However, compulsory admissions also take place when necessary if clients are unfit to make their own decisions and their behaviour is dangerous.

Therapists can ask for consultation about difficult cases any moment. A consulting psychiatrist is always available, and daily case meetings are open to any therapist who faces a problem or feels a case is not progressing. This means there is no principal difference in the quality and availability of services between TAU and Experimental Intervention.

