### Patients in crisis

Another factor is that clients are referred to the team in crisis situations. This means it is a highly vulnerable group of people in desperate circumstances who, as a result of avoidance or resistance, have passed through every safety net and who often function poorly. For those patients, providing reflective feedback focusing on the patient's own situation and the relationship with the mental health services will probably be quite challenging. Otherwise, the service works in shifts, which means that changes in staffing are sometimes inevitable and the standard approach is to work with co-therapy pairings (to safeguard both quality and continuity). So the therapeutic relationship is split up between several people, which might complicate the feedback about the alliance. Finally, the therapists are a mixed group of highly experienced permanent staff (6 psychiatrists, 10 social psychiatric nurses, two psychologists and a system therapist) and relatively experienced doctors (28 years on average, some of whom are being trained as psychiatrists) to work in the team temporarily for an average of six months; this means that specific expertise can vary considerably from therapist to therapist.

Another limitation of the study is that the feedback instrument does not provide information about the influences of social support, changes in the primary domains of a persons life and historical developments concerning the family of origin, which can be of importance for understanding the broader context of the change process [64].

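### Therapist attitude is scheduled only before and after the study, so as written a resident staying about six months would have at most one score and roughly half to 70% of resident groups neither

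*Protocol article*

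**What the plan says.** Procedures and time points fixes two occasions for the therapist questionnaire. The first is set out as "Before the study starts, the therapists are required to complete a one-off questionnaire measuring their attitude to the instrument", together with their motivation to use feedback. The second is: "The same questionnaire will be completed by the therapists after the study period". Neither is tied to a therapist's own arrival or departure.

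The staffing is not fixed. In the section on treatment as usual (TAU): "The team is supplemented by a group of residents that changes every six months". Patients in crisis says that the temporary doctors come "to work in the team temporarily for an average of six months". Residents are listed among the treating therapists, and all therapists work in both conditions.

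Intake lasts two years from October 2009 (Design). For each patient, "The intervention lasts a maximum of six months and stops when treatment ends or after six months", and "The follow-up measurement takes place three months after the end of treatment".

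The abstract's Discussion gives the purpose of the measure: the study also asks whether, and how far, the quality of the alliance and "the motivation of the person delivering treatment with respect to the instruments play a role".

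**The concern.** Two calendar dates suit a stable team. They do not suit one in which part of the staff is replaced several times between those dates. A resident group that arrives after the start and leaves before the end falls between the two measurements.

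The gap is built into the schedule, and it follows experience. Permanent staff can be measured twice; most resident groups may not be measured at all. The article's Conclusion describes the less experienced staff as a sizeable group and suggests that feedback may work less well, or even backfire, in their hands. Design benefits and drawbacks also argues that allegiance is unlikely to favour the feedback (EXP) arm, partly because therapists of differing motivation treat EXP patients. For the intermediate resident groups, neither statement could be examined with the scheduled scores.

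**Working it through.** The article gives no figure for this point, so there is none to reproduce. The check counts resident groups against the two measurement dates.

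**Inputs**
- Length of a resident group's stay: 6 months (TAU section; given as an average in Patients in crisis).
- Study length *T*, which the article does not define for this purpose. Three readings are possible: 24 months (intake only), 24 + 6 = 30 months (plus maximum treatment), or 24 + 6 + 3 = 33 months (plus follow-up).
- Months the first group has already served at study start, *p*: not given, so varied from 0 to 5.
- Assumption: a group has the first score if in post at month 0 and the second if in post at month *T*. When a rotation falls exactly on either date, the group is counted as measured, which favours the plan.

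**Formula**
- Number of groups: *n* = (*T* + *p*)/6, rounded up.
- One group has the first score and a different group has the second, so groups with neither = *n* − 2.

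**Results**

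| *T* (months) | *p* (months) | Groups *n* | Both scores | Neither score |
|---|---|---|---|---|
| 24 | 0 | 24/6 = 4 | 0 | 2 of 4 (50%) |
| 24 | 1–5 | 5 | 0 | 3 of 5 (60%) |
| 30 | 0 | 30/6 = 5 | 0 | 3 of 5 (60%) |
| 30 | 1–5 | 6 | 0 | 4 of 6 (67%) |
| 33 | 0–3 | 6 | 0 | 4 of 6 (67%) |
| 33 | 4–5 | 7 | 0 | 5 of 7 (71%) |

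No six-month group has both scores on any reading; that would take a stay of at least 24 months. The share with neither runs from 50% to 71%. The 50% arises only if the study period means intake alone and rotation coincides with the start.

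Only one group has a score taken before it used the method: one of 4 (25%) at best, one of 7 (14%) at worst.

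Permanent staff listed in Patients in crisis: 6 psychiatrists + 10 nurses + 2 psychologists + 1 system therapist = 19. These therapists can have both scores if they stay throughout.

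**The case against.** Several points on the other side have force.

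- **No motivation analysis is specified.** The two numbered research questions do not mention therapist motivation. Neither the primary analysis nor the multilevel models under Feedback and client and therapist variation and Alliance and outcome include an attitude covariate. A reader might infer that a planned analysis fails, but the article describes none. What remains is the question stated in the abstract, for which this questionnaire is the scheduled therapist measure.
- **The literal reading may not be what was done.** The article says all participants received the same training in the feedback method. With rotating residents, that implies some procedure for newcomers, and the questionnaire may have been part of it. This is possible, but the text ties the form to the start of the study and not to each therapist's start.
- **The absolute claims are too strong.** A reader might infer that no resident could have both scores and that most certainly have none. The six-month stay is also given as an average, so a stay of 24 months or more is not strictly excluded. The number of residents is not given, and on one reading exactly half of the groups have neither score.
- **Groups are not patients.** A reader might infer that patients of unscored residents have no therapist score at all. Treatment is given as far as possible by the same two therapists, and co-therapy is standard, so some of these patients will have a scored permanent co-therapist. How pairs are formed is not stated, so the share of patients affected is unknown.
- **It may be too late.** Two years from October 2009 ends around October 2011, and the article cites work dated 2013. Intake was probably complete when the article was written, so the remedy needs a fallback.

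These points limit the size of the concern. They do not remove the mismatch between the stated time points and the stated rotation.

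**Conclusion.** The point stands as a minor one. As written, the schedule gives a resident who stays about six months at most one attitude score, and leaves roughly half to 70% of resident groups with neither. That range rests on groups of similar size, a six-month stay, a study period of 24 to 33 months, and unknown alignment of rotation with the start. Evidence on therapist motivation would come mainly from the permanent staff, with partial cover for residents' patients through co-therapists.

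The documents do not support extending this to the main result. The primary EXP versus TAU comparison does not use the attitude score, and neither do the sample size calculation or the primary outcome.

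**What to change.** Tie the questionnaire to the therapist and not to the study calendar. Each therapist completes it on joining the team (for those already in post, before the study starts), before treating a first EXP patient, and again on leaving or at study end. Use the joining score in any analysis of motivation, because it precedes that therapist's experience with the method in the trial. A motivation-by-feedback interaction is optional, since the protocol does not plan one. The description of the form as one-off should also go, because the same paragraph repeats it.

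If the measurement window has passed, report which therapists have scores and on which occasion, split by permanent staff and residents, and limit conclusions about motivation to the therapists measured.

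The cost is one changed sentence in the procedures and a 19-item form for each joining and leaving therapist. The fallback needs only a table and a sentence in the report.
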